### Trial oversight

The trial will be overseen by the Trial Management Group (TMG), as well as two fully or partially independent committees, the Data Monitoring and Ethics Committee (DMEC) and the Trial Steering Committee (TSC). Both the TMG and the DMEC/TSC will provide overall supervision of the trial and ensure that it is conducted according to the Good Clinical Practice (GCP) guidelines. The DMEC will monitor data collection, including data quality and safety information. The TSC will be monitoring the overall progress of the trial and ensure that study procedures are conducted in adherence to the protocol. The study investigators will provide trial-related monitoring, audits, and reviews from the Sponsor or the Research Ethics Committee (REC).

### Service user involvement

People with lived experience were involved with both the conception and the development of this project, as well as the conduct of the trial. Trial design was reviewed by the Service User Advisory Group (SUAG) of the NIHR Maudsley Biomedical Research Centre (BRC) which found CRiB2 to address a clinical area of need. Based on their recommendation we decided not to exclude people with a co-morbid personality disorder diagnosis to make the sample more representative. The NIHR Maudsley BRC Feasibility and Acceptability Support Team for Researchers (FAST-R) also reviewed the trial plan and relevant study information. Based on their feedback, we adopted improvement of psychosocial functioning as the trial’s primary endpoint to reflect the prioritisation of functional recovery as an outcome. We also reduced technical language in participant-facing documentation (i.e., information sheet and consent form). In collaboration with Bipolar UK, a focus group was held prior to protocol finalisation which reviewed study procedures and made suggestions to improve trial procedures from a patient perspective (i.e., preventing participant over-burden, improving appointment scheduling, debriefing, and providing feedback).

Two service users are part of our TSC and provide regular feedback on the study conduct and issues arising with its progress. For example, their input informed our procedures for remote data collection (i.e., saliva samples/PANAS) with the aim of making it as simple and non-intrusive for study participants as possible. Service users also offer advice on how to approach potential participants and improve our recruitment strategies. A researcher with BD diagnosis joined the study team at the application stage to support the project from an expert-by-experience perspective. We are in the process of developing an advisory group of service users with experience of BD and representation at each site who will provide advice throughout the trial. They will be involved in data analysis through advisory workshops and dissemination, including as authors of our papers and plain English summaries for the BD community and the wider public.

### Safety monitoring

Potential adverse events (AE), serious adverse events (SAE), adverse reactions (AR), unexpected adverse reactions (UAR), serious adverse reactions (SAR) and suspected unexpected serious adverse reactions (SUSAR) will be monitored and recorded throughout the trial using the AE log in the participant case report form. In addition, therapists will be collecting AE throughout the intervention.

Investigators will assess whether the AE may be related to study participation or therapy and will also assess the severity of the event. Classification of AE as SAE will be based on whether the event: a) results in death, b) is life-threatening, c) requires hospitalisation or prolongation of hospitalisation (not including one for pre-existing condition), d) results in persistent or significant disability, and e) results in an important medical event (IME). All AE will be also reviewed by the DMEC to establish the relatedness to the trial or the intervention and whether these can be classified as SAE/AR/UAR/SAR/SUSAR. All AR and UAR will be reported within 24 h to the CI, as well as be considered in committee meetings. All SAE and SAR will be reported within 24 h by the CI to the Sponsor. Only SUSARs will be reported within 7 days by the CI to the REC for review.

Although we do not anticipate any SARs or SUSARs, participants presenting any such reactions will be withdrawn from the CR intervention and, if not already done by the participant, these reactions will be brought to the attention of their named healthcare professional. AE of any category that have not resolved by the end of the trial, or that have not resolved upon discontinuation of the subject’s participation in the trial, will be followed until it resolves, stabilises, returns to baseline, or cannot be attributed to trial participation or to factors related to the trial.

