### Intervention

Participants in the treatment arm will receive a 12-week course of CR therapy using the online software CIRCuiTS™ (www.circuitstherapy.com). CIRCuiTS™ is a manualised CR approach, developed according to the key principles of CR (e.g., errorless learning, scaffolding, positive feedback, strategy development) [41]. CIRCuiTS™ employs rigorous cognitive training with computerised tasks, emphasises the identification and implementation of useful strategies, supports the development of metacognitive skills, as well as the transfer of cognitive skills and strategies to daily life activities.

CR will be delivered to participants over the 12-week intervention period. Sessions are one-on-one 1-h with the therapist, either in person or remotely (i.e., video call). Additionally, all participants in therapy have access to CIRCuiTS™ for independent sessions, with practice tasks agreed with the therapist. The target for therapy engagement is 2–3 hourly sessions per week aiming at a total of 30–40 sessions over 12 weeks.

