#### Treatment adherence and retention

Following evidence from a secondary analysis of our feasibility study [42], 20 h was defined as the minimum therapy dose. This includes time spent in face-to-face or remote therapist-supported sessions and time spent on independent training. Strategies employed for engaging participants with the intervention involve planning sessions tailored to participant preferences and schedule and sending text reminders ahead of sessions. Individual therapy logs will be used to monitor and record treatment adherence.

Participants will be offered feedback on their baseline neuropsychological test performance after the W25 assessment. In addition, participants allocated to the TAU only group, will be offered access to CIRCuiTS™, as well as a one-off session with a therapist, after the W25 assessment. Each participant will be compensated with £20 for each study assessment, while travel expenses for public transportation or mileage will be reimbursed for all participants.

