#### Treatment as usual

Participants in both trial arms will continue to receive their standard care without any interference from the trial team. Pharmacological and non-pharmacological treatments, as well as any use of healthcare services, will be monitored and recorded for all participants at each post-randomisation visit.

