		**Trial time-points**						
**Procedures/Measures**	**Completed by**	**Screen A (W-2)**	**Screen B (preW0)**	**Baseline (W0)**	**Intervention (W1-12)**	**Post (W13)**	**Follow-up (W25)**	**All (W1-25)**
*Administrative*								
Eligibility assessment	R	x	x					
Informed consent	R			x				
Randomisation	TM			x				
CR delivery	T				x			
Blinding	R					x	x	
*Eligibility*								
Patient information	R	x						
MINI 7	R	x		x ^a^				
TOPF / MoCA-T	R	x						
HAMD / YMRS	R	x	x	x		x	x	
*Interview-based*								
Sociodemographic	R			x		x	x	
Illness history	R			x				
Service use	R			x		x	x	
*Baseline only*								
HAMA	R			x				
CTQ / MEQ / MSI-BPD	P			x				
*Efficacy outcomes*								
Cognitive battery (Hotel test, WMS-IV ^b^, WAIS-IV ^b^, TMT, FAS)	R			x		x	x	
FAST / GAS / EQ5D-3L	R			x		x	x	
PDQ / PSQI	P			x		x	x	
*Mechanistic outcomes*								
Saliva sample	P			x		x		
PANAS	P			x		x		
MAI / Torres	P / R			x		x	x	
*Therapy-related* ^c^								
Therapy log	T				x			
WAI-SR	P & T				x (W3, W12)			
CR satisfaction	TM					x		
*Monitoring*								
Adverse events	R & T			x		x	x	x
Concomitant Tx	R			x		x	x	
Mood monitoring	P							x

*CR* Cognitive Remediation Therapy, *CTQ* Childhood Trauma Questionnaire, *EQ5D-3L* EuroQoL-5 Dimensions – 3 Levels, *FAS* F-A-S letters verbal fluency test, *FAST* Functioning Assessment Short Test, *GAS* Goal Attainment Scale, *HAMA* Hamilton Anxiety Rating Scale, *HAMD* Hamilton Depression Rating Scale, *MAI* Metacognitive Awareness Inventory, *MEQ* Morningness-Eveningness Questionnaire, *MINI 7* Mini International Neuropsychiatric Interview for DSM-5, *MoCA-T* Montreal Cognitive Assessment-Telephone version, *MSI-BPD* MacLean Screening Instrument for Borderline Personality Disorder, *MVAS* Maudsley Visual Analogue Scale, *PANAS* Positive and Negative Affect Schedule, *PDQ* Perceived Deficits Questionnaire, *PSQI* Pittsburgh Sleep Quality Index, *TMT* Trail Making Test, *TOPF* Test of Premorbid Functioning, *Tx* Treatment, *W* Week, *WAIS* Wechsler Adult Intelligence Scale, 4^th^ edition, *WAI-SR* Working Alliance Inventory-Short Revised, *WMS-IV* Wechsler Memory Scale, 4^th^ edition, *YMRS* Young Mania Rating Scale

*Roles:* P: Participant; R: Researcher; T: Therapist; TM: Trial Manager

^a^MINI comorbidity data not required prior to inclusion (e.g., anxiety disorders) will be assessed at W0 instead of W-2

^b^Preselected tests rather than whole scales: WMS-IV: Verbal Paired Associates I & II; WAIS-IV: Digit Span & Coding

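### Therapist collection of adverse events adds a source that only the CR arm has before week 25, so pooled counts of non-serious events by arm would lean towards an excess in CR

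*Protocol article*

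**What the plan says.** The Safety monitoring section sets up two sources. The first covers both arms: AEs of every category "will be monitored and recorded throughout the trial using the AE log in the participant case report form". The second is added to it: "In addition, therapists will be collecting AE throughout the intervention". Table 1 agrees. Its row "Adverse events R & T" names researcher and therapist as the people who record AEs, and it is marked at baseline, W13, W25 and in the column for all of weeks 1–25.

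Three other sections show who can be reached by the second source:

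- **CR arm (Intervention).** "The target for therapy engagement is 2–3 hourly sessions per week aiming at a total of 30–40 sessions over 12 weeks". Under Treatment adherence and retention, therapy time includes independent training as well as sessions with the therapist.
- **TAU arm (Treatment adherence and retention).** TAU participants are offered access to the software, "as well as a one-off session with a therapist, after the W25 assessment". They have no trial therapist before then.
- **Both arms (Procedure; Other measures).** Assessments after randomisation take place at W13 and W25. A weekly self-rated mood scale runs from week 1 to week 24 and is used only to monitor mood and wellbeing.

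**The concern.** A count of AEs by arm is interpretable only if events are looked for equally hard in both arms. Here an extra observer is present in one arm for 12 weeks, and that observer's presence is determined by the randomised allocation. Any AE found only by a therapist adds to the CR count and has no counterpart in TAU.

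Two opposite errors become possible. An excess in CR may be read as harm when it reflects detection, or a real excess may be dismissed as detection. Unless the source of each event is known, the data cannot separate the two. The Stopping rules section sets no formal rule but allows early discontinuation for safety reasons, so safety judgement rests on how such reports are read. The published harms table would carry the same ambiguity.

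**Working it through.** **No stated figure to reproduce.** The article gives no AE rate, AE count or AE power. The stated 90% power for an effect of 0.37 concerns FAST and has no bearing here.

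**AE ascertainment by arm and period, as described**

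| Period | CR + TAU | TAU alone |
|---|---|---|
| Weeks 1–12 | AE log; weekly mood self-rating; therapist collection | AE log; weekly mood self-rating |
| W13 visit | Researcher | Researcher |
| Weeks 13–25 | AE log; weekly mood self-rating to week 24 | AE log; weekly mood self-rating to week 24 |
| W25 visit | Researcher | Researcher |

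The arms differ in one cell only, therapist collection in weeks 1–12. No scheduled AE enquiry is described for TAU in that period to balance it.

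**Illustration 1: event counts.** Assume equal true event rates. In weeks 1–12, 90% of events are captured in CR and a share c in TAU, with c from 0.40 to 0.70. In weeks 13–25 the share c applies to both arms. None of these figures comes from the article.

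- Weeks 1–12: ratio = 0.90/c. For c = 0.70, 0.90/0.70 = 1.29. For c = 0.40, 0.90/0.40 = 2.25.
- Whole trial, with events split evenly between the two periods: ratio = (0.90 + c)/(2c). For c = 0.70, 1.60/1.40 = 1.14. For c = 0.40, 1.30/0.80 = 1.63.

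**Illustration 2: participants with a recorded AE.** Let the true risk be p in both arms, with 125 per arm (Trial design). The common source finds a share d, and therapists find a share t of what it misses, in CR only. This version does not split the trial into periods. Expected counts are 125·p·d in TAU and 125·p·[d + (1 − d)·t] in CR, so the ratio is 1 + t(1 − d)/d.

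- Example with p = 0.5, d = 0.7, t = 0.5 (assumptions). TAU: 125 × 0.350 = 43.8. CR: 125 × 0.425 = 53.1. Ratio 1.21.
- Chance of a nominally significant difference at two-sided 0.05 in that example: the difference is 0.075, and its standard error is √(0.350×0.650/125 + 0.425×0.575/125) = 0.0614. This gives z = 1.22 and a chance of Φ(1.22 − 1.96) = about 23%, although the true risks are equal.
- Over d = 0.5 to 0.9 and t = 0.25 to 0.8 the ratio runs from 1.03 (d = 0.9, t = 0.25) to 1.80 (d = 0.5, t = 0.8).

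The excess falls in CR in every case. Its size depends mainly on how complete the common source is: 1.03–1.09 if it finds 90% of events, 1.25–1.80 if it finds half.

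**After the fix.** If only events found through the common source are compared, both arms have the same expected capture and the expected ratio under equal risk is 1.00.

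**The case against.** The strongest reply is that the article already provides for continuous recording in both arms, plans no between-arm AE test, and leaves tabulation to an SAP that is not shown. Much of this stands, and it rules out several stronger readings that a reader might infer:

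- **That TAU events are sought only at W13 and W25.** Not supported. Table 1 marks AEs across weeks 1–25, and the AE log applies throughout the trial without restriction by arm. The weekly mood rating could also flag deterioration in either arm. What is absent is any description of a scheduled AE enquiry for TAU between baseline and W13.
- **That therapists ask about AEs several times a week.** Not stated. The 2–3 weekly sessions are an engagement target that includes independent sessions, and the article does not say AEs are asked about at each one.
- **That all events go into a single log with no source recorded.** This is a natural reading, but the article does not say where therapist-collected events are entered or whether the case report form already records the source.
- **That a planned safety test is biased, or that the monitoring committee is misled.** No such test is described. The committee's stated task is to judge the relatedness and classification of events, not to compare rates between arms.
- **That the ratio of 1.29–2.25 describes the whole trial.** It covers weeks 1–12 only.

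The appeal to the SAP answers only part of the point. The asymmetry arises in data collection, which the protocol sets. An SAP can choose how to tabulate AEs, but it can separate the sources only if the source was recorded with the event.

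**Conclusion.** The point holds in limited form. By design, therapist collection is an extra AE source confined to CR during weeks 1–12, and nothing described for TAU in that period offsets it. Pooled counts of non-serious AEs by arm would therefore be biased towards an excess in CR. The direction follows from the design. The size does not, because the article gives no AE rates or capture fractions. On the assumptions shown, the apparent ratio with no true difference is 1.29–2.25 in weeks 1–12 and about 1.14–1.63 over the whole trial. It is close to 1 if the common source is nearly complete.

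This does not invalidate every AE comparison. Events elicited with the same questions at W13 and W25 remain comparable. Serious events such as hospitalisations are less affected, since service use is also recorded in both arms at W13 and W25. The primary outcome is not affected. The matter is worth correcting because the remedy is cheap, and because the source of an event is hard to recover if it was not recorded at the time.

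**What to change.** 1. Record the source (researcher visit, therapist, other report) and date of each AE, if the case report form does not already do so. Allow more than one source per event. Otherwise an event told first to the therapist and again at W13 could drop out of the CR count from the common source and bias the comparison the other way.
2. Base any between-arm AE comparison on events elicited with the same questions at W13 and W25 in both arms, plus serious AEs.
3. List therapist-collected events separately as safety information on the CR arm, and keep therapist reporting as it is.
4. Say in the safety report, and to the monitoring committee, that ascertainment in weeks 1–12 differed by arm.

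The cost is one data field, a line of analysis wording and two AE tables instead of one. The between-arm comparison will also leave out non-serious events that only a therapist picked up; these remain visible in the CR listing.

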#### Inclusion criteria

Adults aged 18–65 years;DSM-5 diagnosis of bipolar type I or II (validated using the Mini International Neuropsychiatric Interview [MINI] 7);Euthymic according to the Newcastle Euthymia Protocol, requiring a score of less than 8 on both the Hamilton Rating Scale for Depression (HAMD) and Young Mania Rating Scale (YMRS) covering the entire month prior to inclusion;Ability to use a computerised device (defined as having used a computer, a tablet, or a smartphone at least once in the prior 4 weeks independently).

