#### Withdrawal

Participants can be withdrawn in the event of BD symptom exacerbation, or adverse events associated with the trial or therapy procedures. All participants are free to withdraw from the study at any time, without providing a reason. Similarly, therapy can be discontinued at any point, if a participant withdraws from the trial or decides they no longer wish to continue the intervention. If a participant withdraws from the intervention only, all efforts will be made to continue obtaining follow-up data. Details of any withdrawals and, if possible, reasons for dropping out will be recorded in withdrawal forms.

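### The hospitalisation criterion for serious adverse events has an unqualified exclusion for pre-existing conditions which, as worded, covers unplanned admissions for a bipolar episode

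*Protocol article*

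**What the plan says.** The Safety monitoring section of the protocol article gives five alternative criteria, (a) to (e), for classing an adverse event (AE) as serious. Criterion (c) is met when the event "requires hospitalisation or prolongation of hospitalisation (not including one for pre-existing condition"), and the parenthesis closes there. The article does not define a pre-existing condition. It does not restrict the exclusion to admissions that were planned, arranged before consent, or due to a condition unchanged since entry.

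The exclusion belongs to (c) alone. Criterion (a) is death. The other three are "b) is life-threatening", "d) results in persistent or significant disability" and "results in an important medical event (IME"), and none carries an exclusion. The important medical event in (e) is not defined in the article.

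The same section sends SAEs to the Sponsor within 24 hours. It adds a second look: "All AE will be also reviewed by the DMEC to establish the relatedness to the trial or the intervention", and the sentence goes on to include whether each event is an SAE or a serious reaction.

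Under Inclusion criteria, every participant must have a "DSM-5 diagnosis of bipolar type I or II" and be "Euthymic according to the Newcastle Euthymia Protocol", with the mood-score limits covering the month before inclusion. The Withdrawal section foresees relapse: "Participants can be withdrawn in the event of BD symptom exacerbation". It names this next to adverse events associated with the trial or therapy, not as one of them.

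**The concern.** An exclusion of this kind usually serves to keep planned admissions, for a problem the participant already had and which has not changed, out of expedited reporting. In most trials a loosely worded version affects few events. Here the condition under study is itself the pre-existing condition of the whole sample, so the loose wording reaches the kind of admission that the safety system would most want to see promptly: an unplanned one for mania or depression during the trial.

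Seriousness has consequences in the plan. It decides whether the Sponsor is told within 24 hours. It also decides whether an event judged related to the intervention can be a serious adverse reaction or, if unexpected, a SUSAR that goes to the ethics committee. The Stopping rules section sets no formal rule and leaves early discontinuation for safety reasons to judgement, which makes consistent classification more important. With four sites, an ambiguous criterion invites different readings of the same event.

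**Working it through.** No arithmetic applies. The question is how the stated rule treats one type of event, so the sections are set side by side and the rule is followed through.

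**Inputs**

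| Element | What the article states | Where |
|---|---|---|
| Condition at entry | Bipolar I or II in all participants | Inclusion criteria |
| Mood state at entry | Euthymic over the preceding month | Inclusion criteria |
| Criterion (c) | Hospitalisation counts, except for a pre-existing condition; no qualifier | Safety monitoring |
| Criteria (a), (b), (d), (e) | No exclusion attached | Safety monitoring |
| Consequence of SAE status | Report to the Sponsor within 24 hours | Safety monitoring |
| Second review | DMEC reviews all AEs, including their SAE classification | Safety monitoring |
| Other capture | Service use recorded in both arms at post-randomisation visits (W13 and W25) | Treatment as usual; Table 1 |

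**Following the rule for an unplanned admission with a bipolar episode**

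1. Bipolar disorder was present before consent in every participant, so on the plain meaning of the words it is a pre-existing condition.
2. The participant was euthymic at entry, so the episode is a worsening from baseline. The exclusion makes no distinction between worsened and unworsened conditions, so this does not bring the admission back under (c).
3. Criterion (c) is therefore not met on a literal reading.
4. The admission can still be an SAE. An episode with immediate danger to life meets (b), one with lasting or marked disability meets (d), and an investigator may judge it an important medical event under (e).
5. An admission that is not life-threatening and leaves no such disability rests on (e) alone. As (e) is undefined here, the outcome is a matter of judgement.
6. If the investigator does not class it as an SAE, the 24-hour Sponsor report is not triggered. The event remains an AE. The DMEC may reclassify it, but the article gives no timing for that review and no criteria beyond the same five.
7. The admission also appears under service use, but that record is made at W13 and W25 and is not an expedited route.

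**Result.** Two investigators applying the same text to the same admission can reach different SAE classifications, and the literal reading of (c) points to non-serious. No section of the article says whether such admissions count.

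**Size.** The article gives no rate of admission for bipolar episodes and no split of such admissions by whether they would meet (b), (d) or (e). A number of affected events cannot be derived from it.

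**The case against.** The strongest reply is that the safety system does not depend on (c) alone, and most of that stands.

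- A reader might infer that relapse admissions fall outside SAE reporting altogether. The article does not support this. The exclusion sits on one of five criteria, and an admission for suicidality, for example, could well qualify under (b) or (e).
- A reader might infer that the DMEC would be left without the main safety signal. The article says the opposite: the DMEC reviews all AEs, whatever grade the investigator gave, for relatedness and for SAE and serious-reaction status. Adverse reactions also go to the Chief Investigator within 24 hours, serious or not.
- A reader might infer that a comparison of SAEs between arms would be distorted. The Statistics section describes no such comparison, so no stated analysis is damaged.
- A reader might try to count the missing events. If 2% to 8% of 250 participants were admitted (an assumption with no source in the article), that gives 250 × 0.02 = 5 to 250 × 0.08 = 20 admissions. To call these lost SAEs would further assume that each one fails (b), (d) and (e) and that the DMEC reclassifies none. The article supports neither step.

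It can also be said that the authors probably meant the usual, narrower exclusion, and that the full protocol, which is not shown, may say so. That may be right. But the article does not merely omit a detail; it prints a specific rule whose plain meaning misfires in this population. If the full protocol is narrower, the article misstates it. If the wording is the same, the problem is live in the trial.

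The separate mention of exacerbation in the Withdrawal section adds only a little. It concerns withdrawal and does not say that relapse admissions are not SAEs.

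**Conclusion.** The point holds in a limited form. As worded, criterion (c) does not count an unplanned admission for a bipolar episode, although hospitalisation is the criterion such an event would most naturally meet. What is at risk is the 24-hour report to the Sponsor, and a consistent SAE count, for admissions that meet none of (b), (d) or (e) and that the DMEC does not reclassify. The events themselves are not lost, because they remain in the AE log, in DMEC review and in the service-use record.

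The size cannot be stated from the documents. The conclusion rests on two assumptions: that the words are applied in their plain meaning, and that the full protocol or site instructions do not already narrow them. The primary efficacy analysis and the power calculation are unaffected.

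**What to change.** Amend criterion (c) in two respects. First, limit the exclusion to elective or planned admissions that were arranged before consent for a condition that has not worsened. Second, state that an unplanned admission for a bipolar episode counts under (c). If the full protocol already says this, correct the published wording to match and confirm that all four sites work to the narrower rule.

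Then re-screen the AE log and the service-use records already collected against the new wording, in both arms, and reclassify and report any admission that now meets (c).

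The cost is a short amendment and a check of data already in hand. The downside is a few more SAE forms. No change to sample size, outcomes or analysis is needed.
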